**Preparation for the technique**
□      The student dons sterile gloves.□      The student maintains sterility throughout the procedure.
**Appropriate use of suturing equipment**
□      Needles and tissue are always manipulated with equipment and not with hands.□      The needle is properly held at a point two-thirds from its tip.□      The needle holder is appropriately held with extended index and fourth fingers.□      Forceps are properly held with the student’s nondominant hand.
**Execution of the running subcuticular suture**
□      Orientation of the needle upon insertion is appropriate (at 90º).□      A deep dermal suture is performed on the extreme interior part of the wound.□      The needle is properly exited between the deep dermal knot and the apex of the wound.□      At least three knots are performed, with two loops around the needle holder for the first knot and 1 loop for the remaining knots.□      The student alternates directions at 180º angles when tying the knot.□      For each subcuticular insertion, the needle is properly inserted in the superficial layer of the dermis.□      Each subcuticular insertion is appropriately spaced out.□      Each bite is alternated on one side of the wound to the contralateral wound edge.□      The surgical threads between each bite are parallel to each other.□      A deep knot is performed at the other end of the wound.□      Correct final knot technique is performed with the needle holder.□      The final knot is exited lateral to the apex.
**Best practices**
□      Supination and pronation of wrists is performed.□      The needle is protected at the end of the intervention.□      The student can view the knot when it is cut and the scissors are held at a 45º angle.
**Final knot**
□      Proper tightness of the final knot is obtained.□      The thread is cut at an appropriate length.
**Overall aesthetics**
□      Proper wound tension is displayed (no overlapping of tissues, no gaps).Total: (  )

#### Group 2: Self-Learning

Each student will view eight videos individually and complete the GRS and Subcuticular Suture Checklist for each video as a pretest. Six videos will contain errors and two videos will not. The errors will be technical mistakes in the execution of a running subcuticular suture. Then, for three days, students will have access to a distinct set of videos on GEN to learn how to perform running subcuticular sutures. Three days later, each student will perform a subcuticular suture on a suturing pad and record their first attempt. Finally, students will perform a posttest with the same eight videos shuffled in a different order. The order of the videos will be the same for all students.

#### Group 3: Peer-Learning

Each student will view eight videos and complete the GRS and Subcuticular Suture Checklist for each video as a pretest. Six videos will contain errors and two videos will not. After this initial test, students will interact with other medical students in their group on the GEN platform anonymously for three days. We will display distinct videos on GEN. Comments will be allowed in an interactive format to encourage exchanges. Students will be required to participate in the discussion of at least two videos. Students will not be able to modify their answers on the initial test. Three days later, each student will perform a subcuticular suture on a suturing pad and record their first attempt. Students will interact on GEN and comment on the videos recorded by their peers. On the third day, the students in this group will perform a posttest with the same eight initial videos, but shuffled. The order of the videos will be the same for all students.

#### Group 4: Peer-Learning With Expert Feedback

The details for this group are mostly the same as for group 3; the only difference is that an expert will actively participate in the discussion by commenting on each video on GEN to enhance the students’ educational experience. Although the expert will be anonymous, the students will be able to identify them because they will use the name “expert.” The expert will answer any questions and comment on the discussion to guide the students.

### Study Intervention

In summary (Figure 1), the intervention consists of learning subcuticular sutures on the GEN platform with videos. In groups 1 and 2, there is no peer feedback. In group 3, the participants will learn the suturing skill *on GEN* by collaborating and interacting with each other. They will comment on the videos on GEN (ie, peer feedback). In group 4, the participants will receive peer and expert feedback.

Several gamification elements are integrated into the study to facilitate the interventions. First, the GRS and checklist are installed next to each video; therefore, the students can easily view the videos and properly check every step. Another gamification element in this system is similar to the entertainment, social networking, and news website Reddit, which supports peer-based assessment; peers will be able to comment on the videos, discuss them, and collaborate with each other.

GEN enables the application of a leaderboard. This social comparative feedback component provides learners with information regarding how well they are doing with respect to their peers. This comparative information is provided both individually and in a general context by showing the learner's position on a private individual leaderboard. The learners do not have access to the scores of their peers, avoiding comparisons that could be a detriment to motivation. Learners also obtain access to the number of points they received in each course section through an individual scoreboard.

GEN also provides division of the modules. When the participant has successfully completed one activity, the next activity is unlocked and displayed, much like a video game with successive levels. Moreover, there is a segmented progress bar that allows learners to track their progress in each course and also in each individual course component. As such, the tasks the students are required to complete are clearly displayed, similar to a map, with deadlines; this clearly guides the participants through the activities and completion of the learning material on GEN.

### Study Procedure

#### Objective 1: Evaluate Students’ Ability to Identify the Correct Subcuticular Suture Method

We will determine the best learning method in a virtual environment among the three main groups. We will compare groups 2, 3, and 4: self-learning, peer-learning, and peer learning with expert feedback. There will be no crossovers. Students will undergo a pretest and a posttest to assess the effect of the intervention on their ability to identify the correct way to perform subcuticular sutures. We will also use the control group to compare our intervention to the regular web-based learning method, in which students learn alone by watching different videos with no artificial errors inserted. We will analyze the students’ scoring of each video with the GRS and Subcuticular Suture Checklist.

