**Methods:**

We will conduct a prospective randomized controlled trial with blinding of expert examiners. First-year medical students in the Faculty of Medicine of Université de Montréal will be randomized into four groups: (1) control, (2) self-learning, (3) peer-learning, and (4) peer-learning with expert feedback. Each arm will have 15 participants who will learn how to perform running subcuticular sutures through videos on GEN. For our primary outcome, the students’ ability to identify the correct technique will be evaluated before and after the intervention on GEN. The students will view eight videos and rate the surgical techniques using the Objective Structured Assessment of Technical Skills Global Rating Scale and the Subcuticular Suture Checklist as evaluation criteria. For our secondary outcomes, students will anonymously record themselves performing a running subcuticular suture and will be evaluated using the same scales. Then, a survey will be sent to assess the students’ acceptance of the intervention.

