#### Group 1: Control Group

On GEN, each student will individually view eight videos of an expert performing a running subcuticular suture correctly as a pretest. The Objective Structured Assessment of Technical Skills (OSATS) Global Rating Scale (GRS) (Table 1) and Subcuticular Suture Checklist (Textbox 1) will be made available beside each video, and students will be required to fill out these assessments for each video. For three days, students will have access to a distinct set of videos on GEN to learn running subcuticular sutures. Three days later, each student will perform a subcuticular suture on a suturing pad and record their first attempt. Then, students will undergo a posttest with the same eight videos shuffled in a different order. The order of the videos will be the same for all students.

The OSATS, developed by the University of Toronto, is an accurate and validated method of assessing surgical skills in an operating room setting [33,34]. It comprises a GRS (Table 1) in which certain skills are graded from 1 to 5 (ie, respect for tissue, time in motion, knowledge of instruments, instrument handling, suture skill, flow of operation, knowledge of procedures, and final product).

The checklist is a list of verifications specific to the technique of interest to ascertain whether every step of the procedure was executed (Textbox 1). The checklist was built and revised by a focus group led by the principal investigator, who is the director of the clerkship surgical rotation in the Faculty of Medicine of Université de Montréal. The focus group was composed of one medical student, one junior surgery resident, and one senior surgery resident.

**Table 1 table1:** Global Rating Scores of the Objective Structured Assessment of Technical Skills [8,33,34]. The students will be asked to rate the candidate’s performance on a scale of 1 to 5, and the total score will be summed.

Skill	Potential scores for observed outcomes				
	1-2		3		4-5
Respect for tissue	Frequently used unnecessary force on tissues or caused damage by inappropriate instrument use		Careful handling of tissue, but occasional inadvertent damage		Consistently handled tissues appropriately with minimal damage
Time in motion	Many unnecessary moves		Efficient time and motion, but some unnecessary moves		Clear economy of movement and maximum efficiency

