#### Errors

Each video with errors will include 1 to 3 errors from the list detailed below:

The needle holder is held with the thumb and index finger instead of the thumb and fourth finger.The thumb is entirely inserted in the ring of the needle holder.The needle is not held at two-thirds in the jaw of the needle holder.Suturing is performed at an incorrect depth.Excessive force is used with the forceps.The needle is not inserted at a 90º angle.Sutures are at inappropriate distances.Extra unnecessary steps are performed.The knot is not sufficiently tight.Supination and pronation are not properly performed.The thread is cut at an inappropriate length after tying the knot.The thread is cut without seeing the knot.

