### Statistical Analysis Plan

First, we will perform descriptive statistical analyses to assess the distributions of the variables of interest and determine the appropriate tests to use as well as the need for a potential transformation. Continuous variables with an asymmetric distribution will be described using median (IQR). Categorical variables will be described with proportions. The remaining variables will be described with mean (SD).

In the following paragraphs, we describe our statistical plan assuming a Gaussian distribution.

Objective 1: We will perform balanced one-way ANOVA to compare mean GRS and Subcuticular Suture Checklist scores among all four groups. First, distinct analyses of the pretest and the posttest scores will be performed. Then, the mean difference between the pretest and the posttest scores will be compared using paired *t* tests if the difference between paired values is consistent.

Objective 2: We will perform balanced one-way ANOVA to compare the performance of students in executing a running subcuticular suture as assessed by the GRS and the Subcuticular Suture Checklist.

Objective 3: We will perform descriptive statistical analyses and correlate the study groups with the Likert scales using the Kruskal-Wallis equality-of-population rank test.

Analysis will be performed in RStudio version 1.2.5033 (RStudio Team) [36] and GraphPad Prism version 8.0.0 for Mac OS X (GraphPad Software) [37]. For each analysis, confidence intervals will be calculated for a 95% confidence level. Statistical hypothesis testing will be performed with an alpha threshold of .05.

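### Objective 1 compares the raw points students award to the test videos, which mixes error detection with general severity, so the primary score has no defined direction of benefit

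*Protocol article*

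**What the plan says.** **Construct.** For the primary outcome, the abstract's Methods say that the students' "ability to identify the correct technique will be evaluated before and after the intervention on GEN". The Pretest and Posttest section adds that the test is meant to show whether students spot the inserted errors.

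**Data.** The Objective 1 section says the analysis will use the students' "scoring of each video with the GRS and Subcuticular Suture Checklist".

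**Scoring rule.** The caption of Table 1 has the GRS rated "on a scale of 1 to 5, and the total score will be summed". The checklist textbox awards one point for every step done properly in the video.

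**Test material.** Groups 2, 3 and 4 see the same eight videos in the same order, six with errors and two without. The Errors section says: "Each video with errors will include 1 to 3 errors from the list detailed below". The section on Group 1 gives the control group eight videos that are all correct.

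**Analysis.** The Statistical Analysis Plan section states: "We will perform balanced one-way ANOVA to compare mean GRS and Subcuticular Suture Checklist scores among all four groups". It then says that the "mean difference between the pretest and the posttest scores will be compared using paired" t tests.

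**What no section gives.** There is no reference rating per video, no count of errors found, no separate treatment of faulty and correct videos, and no statement of whether a higher or a lower mean is better.

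**The concern.** The outcome is named as a skill in discrimination, but the variable described is the number of points handed out. For a rater who judges accurately, those points should go down on the items scripted to fail and up on everything else. Training can move both parts at once: a student may learn to see a wrongly held needle and also stop marking down steps that were done well. The two gains push the total in opposite directions.

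Randomisation and pre/post differencing balance or remove a student's starting severity. They do not help when learning itself changes both severity and detection.

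What is at stake is the interpretation of the primary result. A null ANOVA could hide real learning in one arm, and a significant difference would not show which arm identifies errors better.

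**Working it through.** **The plan's own figure.** The article gives no figure for the identification score. Its only related number is the sample size of 13 per group (52 in total), computed on the GRS. The metric of the effect size of 0.8 is not named. Read as a between-group SD of 0.8 with the stated within-group SD of 1.45, f = √(0.64 × 3/4 ÷ 2.1025) = 0.478, which gives 13 per group at 80% power. A two-group t test with d = 0.8 also totals 52. Read as Cohen's f, 0.8 would give 6 per group. On any reading, the inputs are raw GRS scores for suturing performance in an earlier study, not accuracy of rating.

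**Inputs from the article**
- Checklist items, counted by block: 2 + 4 + 12 + 3 + 2 + 1 = 24.
- Videos for groups 2 to 4: six faulty, two correct.
- Errors per faulty video: 1 to 3.

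**Assumptions (not in the article)**
- Each scripted error fails exactly one checklist item, and all other items are done correctly.
- *s* is the chance that a failed item is left unticked (detection). *f* is the chance that a correct item is left unticked (false alarm).

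**Formula.** With e errors per faulty video, the mean number of failed items per video is E = 6e/8, that is 0.75, 1.5 or 2.25 for e = 1, 2 or 3. The expected mean total is

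T = E(1 − s) + (24 − E)(1 − f),

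so the change in T is −E·Δs − (24 − E)·Δf. Better detection (Δs > 0) lowers T and fewer false alarms (Δf < 0) raise it.

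**Cancellation.** Let detection rise from 40% to 80%, so Δs = 0.40.

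| Errors per faulty video | E | Fall in T from detection | Fall in false alarms that cancels it |
|---|---|---|---|
| 1 | 0.75 | 0.3 | 0.3/23.25 = 1.3 points |
| 2 | 1.50 | 0.6 | 0.6/22.5 = 2.7 points |
| 3 | 2.25 | 0.9 | 0.9/21.75 = 4.1 points |

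(The last column is in percentage points.)

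**Direction.** In each row below, discrimination improves at two errors per faulty video.

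| Start (s, f) | End (s, f) | Mean total T | s − f |
|---|---|---|---|
| 0.20, 0 | 0.90, 0 | 23.70 → 22.65 (falls) | 0.20 → 0.90 |
| 0.20, 0.20 | 0.90, 0.05 | 19.20 → 21.52 (rises) | 0 → 0.85 |
| 0.20, 0.10 | 0.90, 0.053 | 21.45 → 21.45 (flat) | 0.10 → 0.847 |

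**Reference raters at two errors per faulty video**
- Perfect rater (s = 1, f = 0): T = 22.5, s − f = 1.
- Ticks everything (s = 0, f = 0): T = 24.0, s − f = 0.
- Ticks each item at random with probability 0.9375: T = 24 × 0.9375 = 22.5, s − f = 0.

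**Control group.** All eight videos are correct, so a perfect rater scores 24. Against 23.25, 22.5 or 21.75 in groups 2 to 4, equal and perfect ability would still show a gap of 0.75 to 2.25 points.

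**GRS.** The same reasoning applies to the eight summed rows (range 8 to 40): lower totals are right on faulty videos and higher totals on correct ones. The article gives no basis for a numerical size.

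**The case against.** **The scoring rule may lie elsewhere.** The article is condensed. The word mean in the analysis section could be no more than the group mean that any ANOVA compares, and how eight videos become one score per student is not spelled out. Because the errors are scripted, marking against them is compatible with the stated intent. A keyed score in a document not shown cannot be excluded. What remains is that the article does fix a scoring rule (summed GRS, one point per correct step) and the comparison of those scores, so the raw total is the natural reading and this is more than an omitted detail.

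**Stronger readings a reader might infer**
- *The mean measures leniency and nothing else.* Not supported. Six of the eight videos are faulty, so a fall is informative if novices start by ticking everything. The mean carries some detection information but cannot separate it from severity.
- *Any harsh rater matches a perfect one.* This holds only at one particular severity, such as the 0.9375 tick rate above.
- *The total is dominated by false alarms.* That needs a false-alarm rate, and the article gives none.
- *Two scripted errors go unmeasured.* Excessive forceps force and unnecessary extra steps have no checklist item, but the GRS rows on respect for tissue and time in motion cover them.

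**The illustration uses chosen inputs.** This is correct: the detection rates and the one-item-per-error rule are assumptions. The first two listed errors, for example, both appear to fall on the same needle-holder item. The opposing signs do not depend on these values. They follow from the scoring rule and the mix of failed and correct items.

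**Conclusion.** The point holds in this form: as published, the Objective 1 analysis compares points awarded without reference to the known content of the videos, and better identification can move that mean in either direction or not at all. Under the stated assumptions, doubling detection from 40% to 80% shifts the checklist mean by only 0.6 of 24 points, and a 2.7 percentage-point improvement in false alarms removes the shift (1.3 to 4.1 across one to three errors). Indiscriminate ticking outscores perfect rating by 1.5 points (24.0 against 22.5). The sizes are illustrative; the lack of a defined direction is not. Since this is the primary outcome and the article reports no recruitment yet, it should be settled before the first student is tested.

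**What to change.** **Checklist, groups 2 to 4.** These are the stated main comparison and see identical videos. For each student, pool the items over the eight videos and define the primary checklist score as sensitivity on the scripted-error items minus the false-alarm rate on the correctly performed items. Higher is better. The key follows from the scripted errors. Compare the groups on this score.

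**Do not use overall percent of items correct.** At two errors per faulty video, 180 of 192 items (93.75%) are correct. Ticking everything therefore scores 93.75%, while 80% detection with 10% false alarms scores (1.2 + 20.25)/24 = 89.4%. On the proposed score these two students get 0 and 0.70.

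**GRS.** Use the student's mean total on the two correct videos minus the mean on the six faulty ones, or the deviation from a reference rating fixed at filming. The difference removes a constant severity shift and also registers excessive force and unnecessary steps.

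**Control group.** Sensitivity is undefined when every video is correct. Report only its false-alarm rate, and leave it out of the keyed comparison unless it is given the same test videos.

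**Cost.** A scoring script, one reference rating of eight videos if that GRS option is taken, and a restated sample-size section, because the present one rests on raw GRS scores. The sensitivity part will be coarse: 12 failed items per student per test at two errors per faulty video (6 to 18 for one to three). The restated calculation should allow for that. Nothing further is asked of the students, unless the control group's test videos are changed.

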#### Pretest and Posttest

All videos will show an expert performing a running subcuticular suture. The expert will be an experienced faculty surgeon licensed by the Royal College of Canada. The expert will only perform the suture without explanation; there will be no sound accompanying the videos. Among the eight videos displayed to students in groups 2, 3, and 4, six will contain technical errors. We will evaluate the students’ ability to identify the errors as they complete the GRS and the Subcuticular Suture Checklist. Participants in groups 2, 3, and 4 will all see the same videos in the same order. The OSATS GRS (Table 1) and Subcuticular Suture Checklist (Textbox 1) will be available beside each video in the pretest and posttest for every student in all four groups.

#### Errors

Each video with errors will include 1 to 3 errors from the list detailed below:

The needle holder is held with the thumb and index finger instead of the thumb and fourth finger.The thumb is entirely inserted in the ring of the needle holder.The needle is not held at two-thirds in the jaw of the needle holder.Suturing is performed at an incorrect depth.Excessive force is used with the forceps.The needle is not inserted at a 90º angle.Sutures are at inappropriate distances.Extra unnecessary steps are performed.The knot is not sufficiently tight.Supination and pronation are not properly performed.The thread is cut at an inappropriate length after tying the knot.The thread is cut without seeing the knot.

#### Objective 2: Evaluate Students’ Ability to Execute a Proper Running Subcuticular Suture

We will determine the best learning method in a virtual environment among the three main groups. We will compare groups 2, 3, and 4: self-learning, peer-learning, and peer learning with expert feedback. There will be no crossovers. Students will receive a suture kit and perform a running subcuticular suture on a synthetic suturing pad. They will record their first attempt and upload it on GEN. One expert will evaluate the students’ performance in the uploaded videos using the GRS and the Subcuticular Suture Checklist. The expert will be a faculty surgeon licensed by the Royal College of Canada. The results will not be published on GEN. The expert will be blinded to the study groups. We will require students to set up their camera field identical to that in the expert videos they will watch on GEN. This will prevent variations in ratings that could occur due to differences in the participants’ setups. More specifically, the learners will be instructed to adjust the field of view of the camera as follows:

Camera location: The camera must face the front and be positioned at a height of 30-50 cm.Field of view: The entire simulator must be visible. Instruments and hands (up to the elbows) must be visible at all times. Students must wear gloves and ensure that there are no objects within the camera’s field of view that can be used to identify them.Resolution and frequency: The camera should be set to 1080p resolution at 24 frames per second.Format: The students are asked to ensure that the videos are captured in mp4 or mov file formats.

We will also use the control group to compare our intervention to the regular web-based learning method in which students learn alone by watching different videos with no artificial errors inserted.

The package of the suture kit will contain an instruction to only open the box while recording the video in which the first attempt at suturing is performed. The student must demonstrate that the package is opened only while recording the video to ensure that they do not practice beforehand. Only the suture pad and the student’s forearms will be shown in the videos to maintain anonymity. Students will not have access to the uploaded videos of the other students.

